#### Sham Lo-TENS group

2.3.2

Participants in the sham group will receive sham Lo-TENS plus routine clinical care (identical to the Lo-TENS group). Sham stimulation uses the same KD-2A device and electrode placement, but the device will be turned off after 10 s of stimulation (to mimic the initial “tingling” sensation of real TENS, ensuring blinding) (30). Participants will remain seated for 30 min per session (matching the Lo-TENS group), 5 days per week, for 4 weeks. Device calibration and electrode checks will be identical to the Lo-TENS group to maintain blinding.

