5. How	The stimulation parameters are set as follows: mode, continuous; waveform, bidirectional asymmetric square wave; pulse width, 200 μs; frequency, 2 Hz. The stimulation intensity in milliamps (mA) will be tailored to the individual’s sensation, permitting slight muscle contraction but ensuring that pain or any discomfort is avoided.	Except there will be no actual treatment, the other setting will be the same as in group 1.
6. Where	The therapy will be performed in the physiotherapy room of the hospitals.	The therapy will be performed in another physiotherapy room of the hospitals.
7. When and how much	Participants in this group will undergo their stimulation in one 30-min session per day, over a period of 5 days per week, for a total of 4 consecutive weeks (resulting in 20 sessions in total).	Except there will be no actual treatment, the others will be the same as in group 1.
8. Tailoring	The stimulating intensity will be tailored to the participant’s tolerance, but without any pain or discomfort.	As no electrical current is delivered, individualized adjustment of stimulation intensity is not applicable. However, participants may adjust their posture to ensure comfort.
9. How well	Intervention adherence will be quantified as the percentage of completed sessions (≥80% adherence defined as successful); assessors are blinded to group allocation to ensure objective outcome measurement.	Same as Lo-TENS group; adherence is quantified as session completion, and assessor blinding is maintained for objective outcome measurement.

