#### Lo-TENS group

2.3.1

Participants in the Lo-TENS group will receive Lo-TENS plus routine clinical care. Routine care includes standard pharmacological treatment (antihypertensives, antidiabetics, lipid-lowering drugs) and lifestyle advice (diet, exercise) per clinical guidelines, with no changes to medication regimens during the study period.

Lo-TENS will be delivered using a KD-2A TENS device (Beijing Yaoyang Kangda Medical Equipment Co., Ltd., China) with disposable self-adhesive electrodes (5 cm × 7 cm). A 2 Hz frequency was selected based on Stein et al., which demonstrated the most robust reduction in sympathetic activity and increase in parasympathetic tone in healthy adults (7); this frequency has also been validated in prior Lo-TENS studies for cardiovascular/metabolic conditions and is well-tolerated in older adults due to minimal muscle contraction (8, 9). Electrode placement on the dorsal metacarpal bones (1st/2nd) and proximal radius muscle belly targets the median/radial nerves (Figure 2), which project to the spinal cord and brainstem regions regulating ANS activity; this placement avoids fragile skin on the trunk/limb extremities (common in older adults) and is easily accessible for clinical delivery (29). The stimulation parameters are: frequency = 2 Hz, pulse width = 200 μs, intensity = 2–5 mA (adjusted to the participant’s maximum tolerable level without pain). Each session lasts 30 min, 5 days per week, for 4 weeks (total 20 sessions).

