#### Blinding

2.3.3

The study is single-blinded: participants are blinded to group allocation, but therapists (who deliver the intervention) cannot be blinded due to the need to adjust TENS intensity. To minimize bias, outcome assessors and data analysts are also blinded to group allocation. A post-intervention blinding effectiveness survey will be administered to all participants (a 5-point Likert scale: 1 = certain sham, 2 = likely sham, 3 = unsure, 4 = likely real, 5 = certain real). The proportion of participants who correctly guess their group allocation will be calculated to quantify unblinding bias, and results will be reported in the trial’s primary analysis.

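### The sham procedure puts participant blinding at risk rather than ensuring it: the intensity-setting step is dropped and the device is turned off after 10 s

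*Protocol article*

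**What the plan says.** **Sham arm, Section 2.3.2.** The same device and electrode placement are used, "but the device will be turned off after 10 s of stimulation", with the aim of reproducing the first tingling "sensation of real TENS, ensuring blinding". After that, "Participants will remain seated for 30 min per session (matching the Lo-TENS group), 5 days per week, for 4 weeks". Calibration and electrode checks are also matched, with blinding given as the reason.

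**Sham arm, Table 1.** Item 5 says that, apart from the absence of treatment, the other settings are as in the active arm. Item 8 says that no current is delivered and that for this reason "individualized adjustment of stimulation intensity is not applicable". Item 6 places sham sessions in a different physiotherapy room.

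**Active arm, Section 2.3.1 and Table 1.** Intensity is "adjusted to the participant’s maximum tolerable level without pain". Table 1, item 5, ties it to the individual's sensation and allows slight muscle contraction. On the schedule: "Each session lasts 30 min, 5 days per week, for 4 weeks (total 20 sessions".

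**Blinding, Section 2.3.3.** Participants, outcome assessors and analysts are blinded. Therapists "cannot be blinded due to the need to adjust TENS intensity". One 5-point survey of perceived allocation follows the intervention, and its result is to be reported with the primary analysis.

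**The concern.** A sham protects the comparison only as far as participants cannot tell which arm they are in. The article matches device, placement, seated time, calibration and electrode checks. It leaves unmatched a step in which an active participant takes part directly: setting the current by how it feels. Table 1 states that this step does not apply to sham, so the difference is asserted by the document and is not a detail lost in condensing it. Turning the device off after 10 s may add a second, visible difference.

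Therapists already know the allocation, so participant blinding carries more of the protection against expectation effects. Table 1, item 1, says the sham is there to separate the effect of stimulation from placebo response, among other things. If sham participants come to suspect their allocation, that separation weakens, and the active-versus-sham contrast would tend to favour the active arm. Because the pilot is meant to supply effect sizes for a definitive trial, any such bias would be carried forward.

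**Working it through.** **1. Schedule and exposure.** Inputs: 30 min per session, 5 days a week, 4 weeks (Section 2.3.1); 10 s of sham stimulation (Section 2.3.2); 2 Hz (Section 2.3.1).

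- Sessions: 5 × 4 = 20, which agrees with the article.
- Session length: 30 × 60 = 1,800 s. Sham stimulation share: 10 / 1,800 = 0.56%. Remaining seated time: 29 min 50 s.
- Over the course: 20 × 10 = 200 s against 20 × 1,800 = 36,000 s.
- Pulses per session: 2 × 10 = 20 against 2 × 1,800 = 3,600.

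These figures describe exposure. They do not measure unblinding, because a sham is meant to deliver little or no current.

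**2. The arms side by side.**

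| Element | Active | Sham | Matched? |
|---|---|---|---|
| Device, electrode placement | KD-2A, both upper limbs | Same | Yes |
| Seated time | 30 min | 30 min | Yes |
| Calibration, electrode checks | Done | Same | Yes |
| Intensity set from the participant's sensation | Yes (2.3.1; Table 1, items 5 and 8) | Not applicable (Table 1, item 8) | No |
| Device state after 10 s | Running | Turned off (2.3.2) | No; whether the participant can see this is not stated |
| Room | Physiotherapy room | Another physiotherapy room | No, but this keeps sham participants from watching active sessions |

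**3. Internal contradiction.** Section 2.3.2 has 10 s of stimulation in the sham arm. Table 1, item 8, says no current is delivered and gives that as the reason for having no intensity adjustment. If there are 10 s of stimulation, that reason fails, and the article does not say how the intensity for those 10 s is chosen. Item 8 also sits badly with item 5, which keeps all other settings the same.

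**4. What the survey could show (illustration only).** The document gives no expected rate of correct guesses, so true rates of 0.6, 0.7 and 0.8 are assumed, with every participant answering and each answer classed as right or wrong. The test is an exact one-sided binomial against 50% guessing, at no more than 0.025.

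| Group | Correct guesses needed | Exact p | Chance at 0.6 | At 0.7 | At 0.8 |
|---|---|---|---|---|---|
| 25 in the sham arm | 18 | 0.022 | 15% | 51% | 89% |
| 50, both arms pooled | 33 | 0.016 | 24% | 78% | 99% |

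Within the sham arm the survey could easily miss moderate unblinding. Pooling the arms helps, but either way the answer comes after all 20 sessions.

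**The case against.** A reader might infer that sham participants meet two plain cues to allocation at each of 20 sessions. The documents do not support that reading, for four reasons.

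- Nothing says that the device has a visible display or timer, or that the participant can see it. Panel position is the sort of operating detail an article may leave to a manual.
- Nothing says that intensity is reset at every session. Only the switch-off after 10 s recurs each time.
- The design is parallel-group with separate rooms, so a missing step reveals allocation only to someone who knows that real treatment includes it. Participants new to TENS may not know. This reassurance is partial, because previous TENS use is not among the exclusions in Section 2.2.1.
- Item 8 of Table 1 rests on a no-current premise that Section 2.3.2 contradicts, so the two cannot simply be added together as one description of the sham.

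Further mitigation is real: assessors and analysts are blinded, FBG and LDL-C are analyser assays, medication is to stay unchanged, and in a pilot it is legitimate to measure whether a sham works.

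These points limit the strength of the claim, but they do not remove it. The absence of intensity adjustment in sham is stated outright, blinded assessors do not protect against a participant's own expectations, and a survey afterwards prevents nothing.

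**Conclusion.** The point holds as a risk to blinding. The article's statement that blinding is ensured is stronger than the procedure supports. One difference between arms is explicit (no intensity-setting interaction in sham); a second, the visible state of the device, is possible but inferred.

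It would go too far to say that blinding will fail, or to treat the 0.56% stimulation share as a measure of unblinding. No bias can be computed from the document. The direction, towards apparent benefit, assumes that participants who suspect sham expect less improvement. Under that assumption office SBP and SF-36 are the outcomes most exposed. FBG and LDL-C are less so, since expectation could reach them only indirectly, for example through lifestyle. The change is worth making because it is cheap and alters no active stimulation parameter, visit or sample size.

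**What to change.** - **Section 2.3.2 and Table 1, items 5 and 8:** use the same scripted intensity-setting routine in both arms, with a mock adjustment in sham.
- **Same places:** screen the device panel from the participant in both arms and, if the device allows it, keep the display on with the output disabled.
- **Section 2.3.2:** replace the claim that blinding is ensured with a statement that the procedure is intended to support it.
- **Table 1, item 8, and Section 2.3.2:** reconcile the statement that no current is delivered with the 10 s of stimulation, so that the sham has one definition throughout.

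The cost is a panel cover, a short script and a minute or two of therapist time per sham session, with no added staff or visits. The loss of sensation after 10 s would remain as a residual cue, to be assessed by the blinding survey already planned.

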#### Blinding

2.3.3

The study is single-blinded: participants are blinded to group allocation, but therapists (who deliver the intervention) cannot be blinded due to the need to adjust TENS intensity. To minimize bias, outcome assessors and data analysts are also blinded to group allocation. A post-intervention blinding effectiveness survey will be administered to all participants (a 5-point Likert scale: 1 = certain sham, 2 = likely sham, 3 = unsure, 4 = likely real, 5 = certain real). The proportion of participants who correctly guess their group allocation will be calculated to quantify unblinding bias, and results will be reported in the trial’s primary analysis.

### Outcomes

2.4

All outcomes are measured at baseline, post-intervention (week 4), and 4-week follow-up (week 8) (Table 2).

**Table 2 tab2:** Timeline for participants’ enrolment, interventions, and assessments.

Time point	Study period							
	Enrolment	Allocation	Intervention					Close-out (follow-up)
	1 week before	0	1st week	2nd week	3rd week	4th week	Post-intervention	8th week
ENROLMENT								
Eligibility screen	X							
Informed consent	X							
Randomization		X						
INTERVENTIONS:								
Lo-TENS + routine clinical management								
Sham stimulation + routine clinical management								
ASSESSMENTS:								
24-h ABPM	X						X	X
FBG	X						X	X
TC	X						X	X
TG	X						X	X
Plasma glucose	X						X	X
HbA1c	X						X	X
HDL	X						X	X
LDL	X						X	X
LDL-cholesterol	X						X	X
24-h dynamic ECG	X						X	X
CRP	X						X	X
Adiponectin	X						X	X
TNF-α	X						X	X
FGF21	X						X	X
Norepinephrine	X						X	X

ABPM, ambulatory blood pressure monitor (the average, standard deviation, maximum and minimum values of patient’s daytime, nighttime, and all-day systolic, diastolic blood pressure, mean arterial pressure, and pulse pressure); CRP, C-reactive protein; ECG, electrocardiogram; FBG, fasting blood glucose; FGF21, fibroblast growth factor 21; HbA1c, glycosylated hemoglobin; HDL, high-density lipoprotein cholesterol; LDL, low-density lipoprotein; LDL-cholesterol, low-density lipoprotein cholesterol; TC, total cholesterol; TG, triglyceride; TNF-α, tumor necrosis factor-α.

#### Primary outcomes

2.4.1

Office blood pressure: Systolic blood pressure (SBP) and diastolic blood pressure (DBP) will be measured using a validated electronic sphygmomanometer (Omron HEM-7121) after 5 min of rest; average of 3 measurements (1 min apart).

Fasting blood glucose (FBG): Venous blood sample (8-h fast) measured via enzymatic assay (Beckman Coulter AU5800).

Low-density lipoprotein cholesterol (LDL-C): Measured via direct enzymatic assay to ensure accuracy in participants with hypertriglyceridemia, a common comorbidity in this population; venous blood sample (8-h fast) analyzed using Beckman Coulter AU5800.

#### Secondary outcomes

2.4.2

24-h ambulatory blood pressure (ABPM): Measured using a Spacelabs 90,217 device (15-min intervals during the day, 30-min intervals at night); primary metrics: 24-h average SBP/DBP, daytime (6:00–22:00) average SBP/DBP, nighttime (22:00–6:00) average SBP/DBP.

Heart rate variability (HRV): Measured via 5-min resting electrocardiogram (ECG) (Philips PageWriter TC50); metrics: time-domain (SDNN, RMSSD) and frequency-domain (HF-HRV, LF-HRV, LF/HF ratio) parameters, analyzed using Kubios HRV software (v3.5) (18, 31).

Inflammatory/metabolic biomarkers: Venous blood samples (8-h fast) analyzed for plasma norepinephrine (NE; enzyme-linked immunosorbent assay [ELISA], R&D Systems), interleukin-6 (IL-6; ELISA, R&D Systems), adiponectin (ELISA, R&D Systems), fibroblast growth factor 21 (FGF21; ELISA, Abcam), and C-reactive protein (CRP; immunoturbidimetry, Beckman Coulter AU5800) (22).

Quality of life (QoL): Assessed using the 36-Item Short Form Health Survey (SF-36); scores range from 0 to 100, with higher scores indicating better QoL.

#### Feasibility outcomes (pilot-specific)

2.4.3

Feasibility outcomes include: (1) Recruitment rate (number of eligible participants recruited per month); (2) Intervention adherence rate (percentage of participants who complete ≥80% of TENS/sham sessions); (3) Attrition rate (percentage of participants who drop out before post-intervention/follow-up); (4) Adverse event rate (number of adverse events related to TENS/sham stimulation) (21).

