### Ethical considerations

2.9

The study protocol is approved by the Ethics Committee of The Second People’s Hospital of Kunming (approval number: 202401011). All participants provide written informed consent. Adverse events (e.g., skin irritation, dizziness) are monitored throughout the study; any serious adverse events are reported to the Ethics Committee and Safety Supervision Committee within 24 h. A Safety Supervision Committee (independent of the study team) oversees participant safety and data integrity. Participants may withdraw from the study at any time without penalty.

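### The adverse event outcome is called a rate but defined as a count, and it keeps only events judged related to stimulation

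*Protocol article*

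**What the plan says.** Section 2.4.3 of the protocol article lists four feasibility outcomes. The first three each carry a time unit or a denominator:

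- Recruitment has a time unit: "1) Recruitment rate (number of eligible participants recruited per month"
- Adherence has a denominator of people: "2) Intervention adherence rate (percentage of participants who complete ≥80% of TENS/sham sessions"
- Attrition has the same kind of denominator: "3) Attrition rate (percentage of participants who drop out before post-intervention/follow-up"

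The fourth does not: "4) Adverse event rate (number of adverse events related to TENS/sham stimulation".

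On who knows the allocation, section 2.3.3 (Blinding) says that "therapists (who deliver the intervention) cannot be blinded due to the need to adjust TENS intensity", and that "outcome assessors and data analysts are also blinded to group allocation". Section 2.3.2 has the sham device switched off after 10 s of each 30-minute session.

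On surveillance, section 2.9 says: "Adverse events (e.g., skin irritation, dizziness) are monitored throughout the study". It adds that "any serious adverse events are reported to the Ethics Committee and Safety Supervision Committee within 24 h", and it names a Safety Supervision Committee independent of the study team. Neither statement is limited to related events.

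Section 3.1 makes a low adverse event rate part of the hypothesis that Lo-TENS is feasible.

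**The concern.** There are two separate weaknesses in one definition.

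**No denominator.** A figure labelled a rate is defined as a number of events. Whether it is low, as section 3.1 expects, depends on whether it is divided by participants or by sessions, and the article does not choose. The choice could then be made after the events are known.

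**Only related events.** Counting an event requires a decision that stimulation caused it. Anyone who knows that a participant received sham has little reason to link an event to a few seconds of current, and has more reason to link the same event to 30 minutes of active stimulation. Dizziness, one of the article's own examples, is hard to attribute in older people taking drugs for blood pressure, glucose and lipids. A comparison of all events between randomised arms does not need that decision; a related-only count does.

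At stake is how far the pilot's tolerability result can be trusted when the definitive trial is designed. The conduct of safety monitoring is not at stake.

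**Working it through.** The article gives no adverse event figure, expected rate or threshold, so there is nothing to reproduce. The check compares the definitions and then illustrates their consequences. Event counts and attribution shares below are assumptions.

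**Inputs from the article**
- 25 participants per arm (section 2.5).
- 20 sessions per participant, 30 minutes each (section 2.3.1).
- 10 s of current per sham session (section 2.3.2).
- 80% attendance as the adherence mark (section 2.4.3).

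**1. Definitions side by side.** Recruitment is per month, and adherence and attrition are percentages of participants. The adverse event outcome alone is a bare number. Section 2.9 collects events without regard to relatedness; section 2.4.3 keeps a subset of them.

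**2. Effect of the open denominator.** Planned sessions per arm: 25 × 20 = 500. At 80% attendance: 0.80 × 500 = 400. Take 5 related events in one arm:
- per participant, if each is in a different person: 5/25 = 20%;
- per planned session: 5/500 = 1.0%;
- per delivered session at 80% attendance: 5/400 = 1.25%.

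The same five events give figures that differ by a factor of up to 20 (20% / 1.0%).

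**3. Effect of the related-only filter.** Current time per session is 10 s in sham against 30 × 60 = 1,800 s in Lo-TENS, or 10/1,800 = 0.56%. Assume 10 events of any cause in each arm, so there is no true difference. Related events = 10 × share attributed.

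| Share attributed, Lo-TENS / sham | Related events, Lo-TENS / sham | Ratio |
|---|---|---|
| 50% / 50% | 5 / 5 | 1.0 |
| 60% / 30% | 6 / 3 | 2.0 |
| 80% / 20% | 8 / 2 | 4.0 |
| 30% / 60% | 3 / 6 | 0.5 |

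The count of all events is 10 against 10 in every row. The related-only count shows a difference in either direction, depending only on attribution.

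**4. Precision at this sample size.** Exact (Clopper-Pearson) 95% intervals for participants with an event:
- 0/25: 0 to 13.7% (upper limit 1 − 0.025^(1/25) = 0.137);
- 1/25: 0.1% to 20.4%;
- 2/25: 1.0% to 26.0%.

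These show why an interval should accompany the figure. They do not measure attribution bias: they would be just as wide for events of any cause, and they overlap heavily.

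**The case against.** The strongest case on the other side is that this is a feasibility item in a pilot, and that counting events caused by the procedure is a recognised measure of tolerability. Much of that case stands, and it limits the point.

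- **Who judges relatedness.** A reader might infer that the unblinded therapists do. The article does not say so. Section 2.3.3 blinds outcome assessors, and section 2.7 has data collected by blinded research assistants at the three assessments. Section 2.7 does not expressly cover events between those visits, so the matter is open. Naming who assesses causality is detail that an article may leave to the full protocol, and its absence is not held against the plan.
- **A biased safety comparison.** A reader might infer that a between-arm test of safety is compromised. Section 2.8 states no such test, and in section 3.1 the comparison with sham belongs to the efficacy claim.
- **Direction.** A reader might infer that the definition flatters Lo-TENS. If active-arm events are more readily called related, Lo-TENS looks worse, not better. The opposite pattern is also possible, and the documents do not settle it.
- **Lost safety data.** A reader might infer that unrelated events go unseen. Section 2.9 monitors adverse events throughout and has any serious event reported within 24 h. Blood pressure and fasting glucose are also measured in every participant as co-primary outcomes, although individual clinical events may not show in group means.
- **Small drafting slip.** Either rate could be computed afterwards if events and sessions are recorded, and no decision rule depends on it.

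What the objection does not remove is the definition itself. The article positively fixes a related-only count and calls it a rate. A fuller document could cure this only by replacing that definition.

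**Conclusion.** The point holds as a cheap improvement to a stated definition. Outcome (4) lacks the denominator that its name promises, and it discards events that the trial already monitors. In this design the discarded part rests on a judgement that knowledge of the arm could influence, and no blinding of that judgement is stated.

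The size of any attribution effect cannot be derived from the article. The ratios of 0.5 to 4.0 above rest on assumed shares and an assumed 10 events per arm; they show that the effect can run either way, not that it will occur. The denominator ambiguity is firmer: the same five events read as 20% or 1.0% using the article's own numbers of participants and sessions, provided the five fall in different people. Neither part is evidence of deficient safety oversight.

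**What to change.** Redefine outcome (4) in section 2.4.3 along these lines:

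> Adverse events of any cause, by arm: participants with at least one event (n/N with exact 95% confidence interval) and number of events per 100 sessions delivered. Serious events are listed individually. Events judged related to stimulation are shown as a secondary column.

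State which participants make up N, for example those who began treatment in each arm. Make the change before events are classified.

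The cost is a sentence or two in section 2.4.3 and one table. The events are already monitored under section 2.9 and session completion is already recorded for adherence, so no extra visits are needed. The downside is a longer table with more background events, which is to be expected in this population.

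Blinded causality review, for instance by the Safety Supervision Committee, is optional. It would add a task that section 2.9 does not assign to the committee, and it is not needed once all events are reported.
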